# LiverCare - a palliative care intervention for patients with liver cirrhosis: study protocol for a multi-center, pragmatic, non-randomised clinical trial

**DOI:** 10.1186/s12904-026-02182-1

**Published:** 2026-06-16

**Keywords:** Advance care planning, Cirrhosis, Interventions, Implementation, Liver disease, Palliative care.

## Abstract

**Background:**

In the transition from compensated to decompensated cirrhosis, median survival decreases from 12 to two years, and patients face some of the highest rates of unplanned hospital admissions. Despite existing recommendations, palliative care is not routinely offered to this population. The aim of this study is to evaluate the effectiveness and implementation of an interdisciplinary palliative care intervention for patients with cirrhosis and their informal caregivers.

**Methods:**

The LiverCare study is a multi-center, mixed-method, pragmatic, non-randomised clinical study with a hybrid type 1 effectiveness-implementation design. The study is conducted in hepatology departments across four hospitals in three of Denmark’s five regions. It is guided by the British Medical Research Council and Reach, Effectiveness, Adaption, Implementation, Monitor frameworks and includes both a feasibility study and a mixed-method process evaluation.

The LiverCare intervention is grounded in a palliative approach, emphasising open, exploratory palliative care conversations. The intervention is integrated into routine outpatient care and the palliative care conversations are delivered by hepatologists and liver nurses who attended a specially designed course within palliative care. Eligible participants are adults with decompensated liver cirrhosis of any etiology who meet at least one general and one disease-specific palliative care indicator, assessed using the Supportive and Palliative Care Indicators Tool. Informal caregivers are invited to participate in the intervention.

Palliative care conversations are initiated following a formal invitation and continue after four to ten weeks and then every six months up to 36 months or until study withdrawal or death. The primary outcome is healthcare utilization, defined as the number and length of hospital admissions, compared to a historic cohort. Secondary outcomes include outpatient contacts, symptom burden, quality of life, and caregiver burden. The study also includes cost-effectiveness and cost-utility analysis.

**Discussion:**

Insights gained from the study will inform future implementation strategies and contribute to the advancement of palliative care practices in hepatology. The results will further support education, training, and competence development for healthcare professionals caring for patients with advanced liver disease.

**Trial registration:**

The study is registered on clinicaltrials.gov (NCT05431946), approved by The Danish Data Protection Agency and reported to the Committee on Health Research Ethics (20222000-31).

## Introduction

Worldwide, liver cirrhosis ranks as the 11th most common cause of death. In 2019, it accounted for an estimated 1.48 million deaths, reflecting an 8.1% increase since 2017 [1]. The distribution of cirrhosis etiologies and their prevalence varies across countries, largely due to differences in lifestyle factors such as alcohol consumption, obesity, and the risk of viral hepatitis. In Europe, alcohol-related liver disease (ARLD) is currently the leading cause of cirrhosis-related deaths [2].

Liver cirrhosis is the end stage of chronic liver disease of all causes, resulting from sustained inflammation that progresses to fibrosis and, ultimately, liver failure. The progression of liver cirrhosis is divided into a compensated stage, characterized by an absence of specific symptoms and apparent complications, and a decompensated stage featuring one or more severe complications such as ascites, hepatic encephalopathy, infection, renal dysfunction, and variceal bleeding [3]. At this stage, the patient often experiences fatigue, nausea, malnutrition and increasing frailty due to loss of muscle mass. This transition from compensated to decompensated liver cirrhosis significantly worsens health-related quality of life (HRQoL) scores [4, 5], while median survival decreases dramatically from approximately 12 years to just two years [6, 7]. Patients with decompensated liver cirrhosis experience some of the highest rates of unplanned hospital admissions, with 1.5 to 3 liver-related admissions per year [8–12].

The current management of decompensated liver cirrhosis focus on symptom relief, the prevention of further complications, and, if possible, liver transplantation, which remains the only curative option [7–14]. According to the World Health Organization, palliative care should be integrated alongside life-prolonging medical treatment as part of a cohesive approach to care, focusing on enhancing the quality of life for patients and their informal caregivers facing the challenges of serious illnesses. Palliative care aims to prevent and relieve suffering through early identification, assessment, and treatment of physical, psychosocial, and spiritual symptoms and concerns [15].

Given the significant symptom burden, poor prognosis, and high caregiver burden, treatment paths with a focus on early identification of palliative care needs, in combination with life-sustaining treatment and care, should be an integrated part of the treatment and care for patients with decompensated liver cirrhosis and their informal caregivers [16, 17]. Despite existing recommendations, palliative care is not routinely offered to patients with cirrhosis [18, 19], highlighting the need for clinical trials to evaluate the effectiveness and implementation of interdisciplinary palliative care pathways [20].

The aim of this study is to evaluate the effectiveness of an interdisciplinary palliative care intervention for patients with liver cirrhosis and their informal caregivers on key outcomes, including hospital admissions, patient symptom burden, quality of life, and caregiver burden. Furthermore, in an integrated process evaluation we will explore key implementation outcomes, mechanisms of impact, and contextual factors that may influence the interventions success.

## Study design

The LiverCare study is a multi-center mixed-method non-randomised intervention study with a hybrid type 1 effectiveness-implementation design, thus taking a dual focus in assessing clinical effectiveness and implementation [21]. The intervention was developed using a pragmatic design with the aim of utilizing existing infrastructure in the implementation [22]. Furthermore, to ensure a comprehensive understanding of the intervention’s functionality and support potential adaptation or replication, a feasibility study and a mixed-method process evaluation will be conducted.

The study design is guided by the British Medical Research Council (MRC) framework for developing and evaluating complex interventions [23]. Since the MRC guidance does not provide an iterative process or specific research designs, we further utilize the Reach, Effectiveness, Adoption, Implementation, and Maintenance (RE-AIM) Framework, which is efficient for evaluating intervention studies [24]. The RE-AIM framework operates at both the individual level (patients and informal caregivers), and the multiple ecologic level (health care professionals and the centres involved in the intervention).

## Method

### Study setting

The LiverCare study is conducted in four hepatology departments covering three of the five regions of Denmark. The hospitals include Copenhagen University Hospital Amager Hvidovre and Copenhagen University Hospital Herlev Gentofte placed in the Capital Region, University Hospital of Southern Denmark, Esbjerg placed in the Region of Southern Denmark, and Aarhus University Hospital in the Central Denmark Region.

The four hospitals comprise a catchment area of 1.6 million citizens, approximately 27% of the Danish population.

In Denmark, all residents have universal, tax-funded access to healthcare services, including general practitioners and specialized hospital care. The healthcare system is organized into a primary sector (general practitioners and municipal health services) and a secondary sector (hospital-based care) [25].

### Participants and eligibility criteria

#### Inclusion criteria for patients are as follows

Adult patients with the diagnosis of cirrhosis of any etiology (clinically, radiologically, or histologically confirmed) as the predominant chronic illness.At least one general and one disease-specific palliative care indicator assessed by the Supportive and Palliative Care Indicators Tool (SPICT).Ability to provide informed consent.Ability to read and understand Danish.

SPICT is a needs-assessment clinical tool developed to identify individuals with serious or advanced illness who are at risk of deteriorating health or dying and who may benefit from palliative care [26]. It supports healthcare professionals in recognising potential unmet palliative needs by combining general and disease-specific indicators, although it does not itself determine the exact nature or severity of those needs. In this study, patients were eligible for inclusion if they had at least one general and one disease-specific SPICT indicator.

#### Exclusion criteria include

Inability to provide informed consent or comply with the study protocol.Diagnosis of advanced malignant disease other than hepatocellular carcinoma.Current contact with specialised palliative care services or hospice.Being listed for liver transplantation.

Eligible patients are invited to participate by a hepatologist or specialised liver nurse, either during hospitalisation or at an outpatient visit. Participation is voluntary, and patients are informed that they may withdraw consent at any time. Patients are encouraged to nominate an informal caregiver to participate in the study. Informal caregivers can include family, close friends, or any other person chosen by the patient. To be eligible, the informal caregiver must be at least 18 years old, be able to speak and understand Danish, and available to participate in at least one study visit. After receiving oral and written information, patients are given at least 24 h to consider participation. If the patient agrees, the first study appointment is scheduled.

## Intervention

### Intervention framework

The intervention is grounded in the modern palliative care paradigm, originating in Cicely Saunders’ concept of “Total pain,” which recognises that suffering has physical, psychological, social, and existential dimensions. These dimensions are interdependent; symptoms are never solely biological but are shaped by personal experience, relationships, and processes of meaning-making. This multidimensional perspective highlights the need to support not only patients but also their informal caregivers, who frequently experience substantial strain when a loved one is seriously ill [27].

Central to the intervention is a person-centred orientation that aligns with the “Platinum Rule” - treat others as they wish to be treated [28]. This requires an understanding of individual values, needs, preferences, and concerns, and a communication approach that actively elicits and responds to these.

To operationalise the palliative approach, the intervention employs the 4-2-4-2 model [29]. Originally developed for chronic lung disease, the model is diagnosis-agnostic and applicable across progressive illness trajectories.

The first four (4–2–4–2) describes four prognostic trajectories as either chronic, early progressive, late progressive, and imminently dying, each associated with distinct goals of care.

The first two (4–2–4–2) denote two forms of knowledge essential in palliative care: objective (e.g., biomarkers, imaging, patient-reported outcomes) and tacit or experiential knowledge that arises through human interaction. Both are necessary for establishing trust, understanding suffering, and tailoring conversations and decisions to each patient and their informal caregivers [30].

The second four (4–2–4–2) revisits the four dimensions of suffering central to the total pain concept: physical, psychological, social, and existential.

The final two (4–2–4–2) refers to the two professional roles required in palliative care: a problem-solving role when suffering is linked to reversible causes, and a companion role when distress arises from irreversible disease processes.

Building on the 4-2-4-2 model, the intervention incorporates an approach to Advance Care Planning (ACP) that operationalises these principles in structured, value-based *palliative care conversations* with patients and informal caregivers. For this study, an approach to ACP that emphasises open, exploratory conversations inviting patients and informal caregivers to share fears, hopes, personal values, and reflections has been adopted. Accordingly, ACP is used not only to discuss treatment ceilings and preferences for end-of-life care, but also to explore broader emotional and existential concerns arising in the context of advanced illness. This expanded orientation reflects the complex and often distressing situations faced by patients and informal caregivers. These conversations are intended to inform the overall plan of care and to ensure that patients and informal caregivers are approached with respect for their values, needs, and dignity.

### Intervention elements

The intervention is delivered alongside standard care and integrated into patients’ regular clinical appointments. In all participating settings, standard care involves routine follow-up of patients with cirrhosis by a team of hepatologists and specialised liver nurses. Following an admission due to decompensated cirrhosis, patients are routinely offered planned follow-up in an outpatient clinic.

The initial palliative care conversation is conducted by a hepatologist in collaboration with a specialised liver nurse. Alternatively, the conversation may be conducted solely by the liver nurse. Subsequent conversations are conducted by either a hepatologist or a liver nurse after 4–10 weeks, and at 6, 12, 18, 24, 30, and 36 months, or until withdrawal from the study or death. Extra visits may be scheduled if clinically indicated or if the patient or informal caregivers request additional support or planning.

#### Invitation

Patients and their informal caregivers receive an oral invitation to take part in a palliative care conversation about living with cirrhosis and future care preferences.Patients and informal caregiver receive a written invitation leaflet designed to support reflection ahead of the conversation.Informal caregivers receive written information outlining caregiver participation, acknowledging the burden of caregiving, and providing information on available support services.

#### Palliative care conversations

Each conversation begins with the healthcare professional setting the stage and clarifying the purpose of the conversation, distinguishing it from routine clinical consultations.The conversation addresses individuals’ concerns across the physical, psychological, social, and spiritual domains. It is a collaborative process between patients, informal caregivers, and healthcare professionals to assess and identify problems and symptoms. The patient and caregiver determine the topics discussed and hold most of the speaking time.Responses from thorough symptom assessment using the PRO-Pall questionnaire are actively used in the conversation [31]. If the questionnaire has not been completed beforehand, it may be completed during the visit.Key topics in the conversations include the daily lives of patients and their informal caregivers, their understanding of the illness, and their hopes and concerns. The conversations provide patients with an opportunity to reflect on what matters most to them, their core values, and their thoughts about future care and treatment.Future care is planned, along with actions to be taken based on conversations with patients and informal caregivers, and a timeframe for follow-up is set.

#### Documentation and actions

The Palliative Care Conversations conclude with a summary of the main points, including agreed-upon care goals and priorities. These are documented in the medical record to inform ongoing care.Based on the conversation, the healthcare professional may initiate relevant actions, including but not limited to:Pharmacological treatment adjustments or medication titration.Referral to psychosocial support services (e.g., chaplain, psychologist).Referral to primary care, rehabilitation services, specialized palliative care teams, or hospices.Coordination or communication with informal caregivers, primary care providers, or public services.

## Study overview

The LiverCare study comprises five Phases, see Fig. 1.

**Fig. 1 Fig1:**
[figure not shown]
Overview of the LiverCare study

### Phase 0: intervention development

The intervention was developed by the LiverCare Consortium in collaboration with palliative care experts. The LiverCare consortium consists of hepatologists and specialised liver nurses with both clinical and research expertise from the four participating departments, and was established to support a national initiative for palliative care in hepatology.

### Phase 1: education of health care professionals

All healthcare professionals involved in the palliative care intervention attend a specially designed one- or two-day course with a focus on theoretical and practical education and training within palliative care, communication, thorough symptom assessment, PRO-PALL questionnaire [31], ACP, and the 4-2-4-2 model [29, 32]. The education and training were facilitated by palliative care experts and professional actors.

### Phase 2: feasibility study

A mixed-method feasibility study will be conducted to assess whether the palliative care intervention is suitable for further testing in Phase 3. The study will include 40 patients (approx. 10 from each department) and their possible informal caregivers. Findings will be reviewed to adjust and refine the intervention and data collection methods in Phase 3.

### Phase 3: intervention study

A total of 240 patients and possible informal carergivers will participate in the palliative care intervention. The intervention will be initiated following completion of Phase 2, incorporating any adjustments identified during the feasibility phase.

### Phase 4: process evaluation

A mixed method, multistakeholder process evaluation is integrated throughout the study. The process evaluation will be conducted to provide both general and specific recommendations for the continued implementation of the intervention.

## Data collection and outcomes

The data collection and outcome measures are categorised into effectiveness and implementation outcomes, aligned with the research questions.

### Baseline and clinical data

At baseline, sociodemographic data will be collected on participants’ age, gender, highest completed level of education, employment status, housing conditions, family relations, support received from the primary sector, and complicating factors such as substance abuse issues, social network difficulties, financial problems, and housing instability. Additionally, disease-related information will be gathered, including cirrhosis etiology, year of diagnosis, complications, and comorbidities. At each study visit, the patient’s current clinical status will be assessed with particular attention to the severity of cirrhosis-related complications and overall frailty, evaluated using the Clinical Frailty Scale [33]. Liver disease severity and prognosis will be evaluated by calculating the Child-Pugh and Model for End-Stage Liver Disease (MELD) scores [34, 35].

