### Effectiveness outcomes

#### Primary outcome

*Healthcare system burden*, measured as the number and length of hospital admissions from the initial visit to death or study exit. Data on health care utilisation will be prospectively recorded by registering events since the last visit at each study visit and compared to a recent historic cohort of a similar size from the involved centers.

Hospital admissions will be categorised into three mutually exclusive groups:

*Liver-related admissions*: inpatient stays of ≥ 24 h due to complications of liver cirrhosis, including variceal bleeding and other bleeding related to portal hypertension, hepatic encephalopathy, spontaneous bacterial peritonitis, hepatorenal syndrome, alcoholic hepatitis, ascites, infection, electrolyte imbalances, increasing frailty, sarcopenia, or poor nutritional status.*Non-liver-related admissions*: inpatient stays of ≥ 24 h for conditions not directly related to cirrhosis.*Short admissions*: hospital stays of < 24 h, excluding admissions in which paracentesis is the sole intervention.

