### Implementation outcomes

An overview of the process indicators and methods of measurement for the feasibility study and process evaluation are presented in Table 1.

**Table 1 Tab1:** Overview of process indicators and methods of measurement and data collection

Domain	Method	Process indicators	Data sources
Reach and uptake	Descriptive quantitative evaluation	Number of patients referred for the intervention Number of patients included of all eligible Referral patterns	Screening data
Effectiveness	Preliminary quantitative evaluation of endpoints in Phase 2 and quantitative evaluation of endpoints in Phase 3 Cost-effectiveness analysis Cost-utility analysis	Number and length of hospital admissions Patient reported outcomes Change in caregiver burden Staff time, training, materials Healthcare utilization QALYs gained	Medical records PRO-Pall EQ-5D-5 L ZBI Danish DRG tariffs EQ-5D-5 L
Adoption		Proportion of sites offering the intervention	Information from study sites
		Differences in implementation between implementation sites	
*Implementation:* Feasibility: *The degree to which the intervention can be carried out in a given setting.*	Mixed-method evaluation Descriptive quantitative evaluation Qualitative evaluation	Resource utilisation Palliative care planning processes No. of invitation leaflets handed out to participants and families No. of palliative conversations per participant No. of informal caregivers participating in palliative conversations. No. of PRO-Pall questionnaires completed for each palliative conversation. No. of medical interventions. No. of patients referred to palliative care teams No. of patients referred to hospices No. of patients referred to municipal offers (exercise, nutrition, alcohol treatment, etc.) Patient experience Caregiver experience Healthcare personnel experience	Self-developed questionnaire with open-ended questions on experiences with palliative care, pre-study training, and the intervention
*Fidelity: The degree to which the intervention was implemented as intended.*			Informal conversations with health care professionals
Acceptability and Appropriateness: *The perception among implementation stakeholders that a given intervention is agreeable*,* palatable*,* or satisfactory.*			Semi-structured interviews informal caregivers and patients
			Medical records
			Semi-structured qualitative interviews

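### Hospital use before entry is not named as a baseline variable for either cohort, and the stated primary comparison is unadjusted, so a prior difference in bed-days would pass in part into the estimated effect

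*Protocol article*

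**What the plan says.** All references are to the protocol article.

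- *Baseline and clinical data* lists sociodemographic and social items in some detail, and then: "disease-related information will be gathered, including cirrhosis etiology, year of diagnosis, complications, and comorbidities". Frailty is scored at each study visit, and "Liver disease severity and prognosis will be evaluated by calculating the Child-Pugh and Model for End-Stage Liver Disease (MELD) scores". Admissions or days in hospital before entry are not named.
- *Primary outcome* defines the outcome as "measured as the number and length of hospital admissions from the initial visit to death or study exit". The recording rule is that utilisation is "prospectively recorded by registering events since the last visit at each study visit". At the first study visit there is no last visit, so the rule as worded captures nothing earlier.
- The comparator in the same section is described as "compared to a recent historic cohort of a similar size from the involved centers".
- *Exclusion criteria* (the recruitment paragraph) says that patients may be invited "either during hospitalisation or at an outpatient visit".
- *Statistical methods* states unpaired t-tests or Wilcoxon-Mann-Whitney tests for numerical between-group comparisons. It names no covariate adjustment or matching.
- Table 1, in the Effectiveness row, gives these data sources: "Medical records PRO-Pall EQ-5D-5 L ZBI Danish DRG tariffs EQ-5D-5 L". Medical records are therefore already a source for the effectiveness endpoints.

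**The concern.** Without randomisation, the similarity of the two cohorts has to be shown. When the outcome is days in hospital, the most direct check is how many days each cohort spent in hospital before follow-up began. Earlier use is also a plausible predictor of later use. A plan that neither tabulates it nor adjusts for it leaves any prior difference in the primary estimate.

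Two features of this trial add weight.

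- Recruitment can take place during an admission or at an outpatient visit. Recent hospital use at entry therefore depends on how patients are picked up, and the article does not say how the starting point is set for historic patients. The direction of any resulting bias cannot be told from the text.
- Some listed variables, such as frailty scored at study visits and the social difficulties, may be hard to reconstruct for historic patients, who had no study visits. Past admissions should be obtainable from records in the same way for both cohorts, which makes them one of the more comparable covariates on offer.

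At stake is a planned effect of 2 days per year. A carry-over of even part of a day is a sizeable fraction of that.

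**Working it through.** **Inputs from *Sample size*:** control mean 7 days/year, reduction 2 days/year, SD 7 days, 199 required, 20% attrition, target 240.

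**Assumed, because the article does not give them:** two-sided 5% level, 80% power, the correlation ρ between prior-year and follow-up days, and any prior-year imbalance D.

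**1. The plan's own figure.** For two groups, n per group = 2(1.96 + 0.8416)² × 7² / 2² = 192.3, so 193. The t-based version gives 193.3, so 194. The stated 199 is within 3% of 194 when read as a per-group size against an equally large historic cohort. At 199 per group, power is 81.3%. No stated figure depends on a baseline value of the outcome.

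**2. Power without adjustment.** 240 × 0.80 = 192 analysed. With 192 in each group, SE = 7 × √(2/192) = 0.714, 2/0.714 = 2.80, and power = Φ(2.80 − 1.96), or about 80%.

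**3. Power with prior days as a covariate.** Residual SD = 7 × √(1 − ρ²).

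| ρ (assumed) | Residual SD | n per group for 80% | Power at 192 per group |
|---|---|---|---|
| none | 7.00 | 193 | 79.9% |
| 0.2 | 6.86 | 185 | 81.5% |
| 0.3 | 6.68 | 175 | 83.5% |
| 0.4 | 6.42 | 162 | 86.3% |
| 0.5 | 6.06 | 145 | 89.8% |
| 0.6 | 5.60 | 124 | 93.8% |

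These are normal approximations. The t-based values differ by a few tenths of a point (83.3% at ρ = 0.3, 89.7% at ρ = 0.5).

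**4. Carry-over of a prior imbalance.** With equal SDs in the two periods, the slope of later on prior days equals ρ, so the unadjusted difference shifts by about ρ × D. For a hypothetical D of 2 days:

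- ρ from 0.3 to 0.5 gives 0.6 to 1.0 day, which is 30% to 50% of the planned effect;
- ρ from 0.2 to 0.6 gives 0.4 to 1.2 days.

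**5. What these figures do not measure.** Steps 3 and 4 compare adjustment for prior days with no adjustment at all. If the analysis already adjusted for Child-Pugh, MELD, frailty, complications and comorbidities, the relevant quantity would be the partial correlation, and the remaining variance would be multiplied by one minus its square. A partial correlation of 0.2, for example, removes 4% of that variance, against 9% to 25% for 0.3 to 0.5. The documents give no basis for choosing a value.

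**The case against.** **This is a condensed article.** The disease-data list is worded as open-ended. The full field list and the model covariates commonly sit in a full protocol, case report form or analysis plan that is not shown. This stands as a caution: prior hospital use may be specified elsewhere. It does not remove the point, because the article does state the baseline data in detail, the start of outcome recording and the between-group tests. Followed as stated, those leave a prior difference in the estimate.

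**Is the adjustment impossible?** A reader might infer that prior bed-days can be neither compared nor adjusted for. The documents do not support that. Medical records are a named source, the historic cohort comes from the participating centres, and nothing rules out a look-back for either cohort.

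**Does the outcome lack a required baseline?** A reader might also set the primary outcome against the questionnaires, all of which have a baseline or pre-intervention measurement. Those are defined as change outcomes and need one. A count of events over follow-up does not, and comparing follow-up use alone is a legitimate choice of endpoint. Prior use matters here as a confounder and covariate, not as a missing part of the definition.

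**The figures rest on assumptions.** This stands. Neither ρ nor a 2-day imbalance is in the documents. Using 192 per group also applies attrition to the historic cohort. With 192 against 240, SE = 7 × √(1/192 + 1/240) = 0.678, 2/0.678 = 2.95, and unadjusted power is already about 84%. Follow-up ends at death or study exit, so an equal-variance calculation is only indicative.

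**Change scores carry their own risk.** This also stands. If the prior year includes the admission at which a patient was recruited, a fall afterwards is expected without any intervention. A comparison of change is then misleading unless entry is defined alike in both cohorts.

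**Conclusion.** The point holds as a worthwhile improvement to the stated plan, not as an error in a stated figure. The article names no pre-entry hospital use for either cohort and describes an unadjusted comparison with a non-randomised historic cohort, so part of any prior difference in bed-days would appear as treatment effect, in either direction.

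The size can only be illustrated. Against an unadjusted analysis with 192 per group and a two-sided 5% level, an assumed correlation of 0.3 to 0.5 would raise power from about 80% to 83-90%. A hypothetical 2-day prior-year imbalance would shift the estimate by about 0.6 to 1.0 day of the planned 2. The gain beyond the severity measures already listed would be smaller and cannot be derived from the documents.

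**What to change.** 1. Add to *Baseline and clinical data*, for both cohorts: number of admissions and days in hospital in the 12 months before time zero, taken from medical records with the admission categories given under *Primary outcome*.
2. Define time zero in the same way in each cohort, and record whether the patient was in hospital at entry.
3. Report prior admissions and days side by side in the baseline table.
4. Include prior days as a covariate in the primary comparison, fixed before outcome data are compared.
5. Keep a comparison of change from prior year to follow-up as a sensitivity analysis only, and say that it is open to regression to the mean.

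If a full protocol or analysis plan already contains this, a sentence in the article pointing to it is enough.

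The cost is one look-back in records that the trial already uses, a few database fields and some analysis wording. No extra patients or visits are needed.
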